## Abstract

**Background:**

Therapies that significantly improve the neurological and functional recovery of individuals with spinal cord injury (SCI) are still urgently needed. The ketogenic diet (KD) has been shown to improve forelimb motor function in an SCI rat model, likely by reducing inflammation and cell death in the spinal cord. Furthermore, our recent pilot study in patients with SCI showed that, compared with a standard hospital diet (SD), 5 weeks of KD started during acute care improved upper extremity motor function and reduced serum levels of a neuroinflammatory blood protein. The primary goals of the current study are to: 1) show the safety and feasibility of administering a KD during acute care for SCI; 2) determine if consuming 5 weeks of a KD significantly improves motor and sensory functions, functional independence and glycemic control; and 3) quantify serum biomarkers that are linked to improvements in neurological recovery and functional independence via targeted proteomics.

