### Procedures to quantify serum biomarkers that may be linked to improvements in neurological recovery and functional independence

#### Sample processing

Serum samples are processed using disposable affinity-depletion cartridges (NorGen Biotek Corp.) that remove the major serum proteins albumin, α-antitrypsin, transferrin and haptoglobin [32]. Protein samples are evaporated and resuspended in 6 M urea, 100 mM Tris buffer at 10 mg/ml. Aliquots of the affinity-depleted serum are reduced using dithiothreitol (25 mM) at 50°C for 30 min followed by alkylation of free thiol groups with iodoacetamide (55 mM) for 30 min in the dark at room temperature. Solutions are then diluted 1/10 in double-distilled water (ddH_2_O) and overnight digestion is carried out using mass spectrometry (MS)-grade trypsin (0.2 μg/μl). The digests are evaporated to dryness in a Speedvac and then resuspended in 50 μl ddH_2_O with 0.1% formic acid.

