#### SWATH-MS analysis

Individual samples are analyzed by the same nanoLC-ESI-MS/MS method described above. SWATH data [35] are collected in 1.8-s duty cycles—a 200-ms time-of-flight survey scan from m/z 400–1250 followed by 32, 50-ms successive tandem mass spectra using 25 m/z mass windows. The MS/MS data are deconvoluted and processed using PeakView™ 1.2 with the SWATH application (SCIEX). This software uses a pregenerated protein identification library to construct individual peptide signatures with fragmentation patterns after analyses for protein identifications. In addition, the areas of the peptide peaks in the MS/MS spectra are used for protein quantification. Identification of proteins associated with the phenotypes being studied will be carried out by univariate (volcano plots) and multivariate (principal components and partial least squares-discriminant analysis) analyses and associated heat-maps.

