### Statistical analysis

Statistical analyses for neurological recovery will include comparisons of means of motor and sensory function, functional independence and serum measurements (e.g., glucose, insulin, alanine aminotransferase and aspartate transaminase) between the two groups, as well as comparisons within each group of the changes from baseline to rehabilitation to discharge (which should take approximately 5 weeks). Descriptive statistics, including measures of central tendency (sample mean, sample median) and dispersion (variance) will be calculated for each group. For safety outcomes, instead of comparing the two groups to the established standard safety values, we will compare circulating levels of proposed outcomes at the various time points among the two groups. If there are no significant group differences in these outcomes, we will conclude that the KD intervention is safe. We will also calculate 95% confidence intervals for the mean group differences for these outcomes as an additional check on safety and feasibility. The primary method of analysis will be analysis of covariance (ANCOVA), regressing the 5-week outcomes (safety, motor and sensory recovery, functional independence, and glycemic state) on the randomly assigned diet, baseline values of the measures, and other covariates such as age and sex. Repeated measures ANCOVA will also be used. Statistical assumptions will be assessed using box plots, residual plots and normal probability plots. Secondary analyses, accounting for all time points, will be conducted using mixed linear models, including repeated measures models. An appropriate structure for the covariance matrix (e.g., the unstructured covariance matrix) will be selected for these models using the final data. When a model term is statistically significant, the Tukey–Kramer multiple comparisons test will be used to determine which specific pair of means are significantly different. This method will allow us to compare changes over time (within-group changes) and differences between groups simultaneously. Covariates (e.g., length of enteral and solid feeding and length of stay in acute and rehabilitation care) will be accounted for in these analyses. Overall cross-sectional between-group comparisons, such as baseline comparisons used to examine pretest parameters, may be performed using the two-group *t* test, and overall within-group comparisons may be performed using the paired *t* test. If assumptions of normality of distribution for the above tests are not tenable, variables may be transformed prior to analysis, or appropriate nonparametric tests, such as the Wilcoxon rank-sum and signed-rank tests, may be used. Statistical tests will be two-sided and will be performed using a 5% significance level. Stratified analyses accounting for different injury levels will also be performed. These analyses will be specific to the distribution of data in each individual subgroup, which will minimize heterogeneity and allow us to analyze subgroups that may be more statistically homogenous and clinically relevant. SAS software, version 9.4 or later, will be used to conduct the statistical analyses. Multiple imputation methods will be used to address missing data for variables with moderate amounts of missing data (≥10%) and after examining whether data are missing completely at random, missing at random, or missing not at random. Missing data analysis will not be performed on variables with <10% missing data to avoid statistical bias larger than that obtained through the use of complete case analysis.

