
For microbiome analysis, alpha diversity indices will be analyzed using linear mixed-model with time (pre- and post-) and group (KD and SD) as fixed factors and participant as a random effect. Permutational multivariate analysis of variance testing will be used to assess the effects of time, treatment, and time × treatment on beta diversity indices. The principal coordinate analysis will be performed to visualize the beta diversity distance matrices [18].

For targeted proteomics, three specific analytic approaches will be utilized. First, two-sample *t* tests, or Wilcoxon rank-sum tests if the normality assumption is questionable, will be used to examine differences in the number of selected peptides and proteins between diet groups at discharge (approximately 5 weeks). Because of the number of proteins to be examined, a false discovery rate of 0.2 will be used to account for multiple hypothesis tests. The second approach will examine the manner in which levels of selected peptides vary across the longitudinal time points of baseline, rehabilitation and discharge. To examine these patterns, mixed linear models such as repeated measures models using time as a within-person factor and diet as a between-person factor will be constructed. Finally, Pearson’s correlation will be used to measure the strength and direction of linear associations between selected peptide levels and 5-week outcomes of safety, neurological, functional and glycemic status. 

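### The targeted-proteomics step meant to find proteins linked to improvement correlates peptides with week-5 outcomes and states no baseline adjustment

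*Protocol article*

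**What the plan says.** The Abstract and the end of the Background section of the protocol article set the third goal as to "quantify serum biomarkers that are linked to improvements in neurological recovery and functional independence via targeted proteomics". The heading of the laboratory procedures is softer: "serum biomarkers that may be linked to improvements in neurological recovery and functional independence". The section on outcome measures lists serum biomarkers by targeted proteomics as the fifth primary outcome.

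The Statistical analysis section then fixes the methods: "For targeted proteomics, three specific analytic approaches will be utilized".

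- The first compares the diet groups at discharge by t test or rank-sum test.
- The second follows peptide levels over the three visits: "mixed linear models such as repeated measures models using time as a within-person factor and diet as a between-person factor will be constructed".
- The third uses Pearson's correlation to "measure the strength and direction of linear associations between selected peptide levels and 5-week outcomes of safety, neurological, functional and glycemic status".

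Earlier in the same section, the main ANCOVA regresses the 5-week outcomes "on the randomly assigned diet, baseline values of the measures, and other covariates such as age and sex". The SWATH-MS section has a separate, untargeted step: "Identification of proteins associated with the phenotypes being studied will be carried out by univariate (volcano plots) and multivariate" methods.

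**The concern.** The goal is about improvement, but the analysis is about the level reached. In the ANCOVA sentence the 5-week outcome is the dependent variable and the baseline value is a separate regressor, so the natural reading of the term is the week-5 value. The correlation takes over that term without the baseline.

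Eligibility runs from C5 to T12 and from AIS A to C, so starting motor, sensory and SCIM scores will differ widely, and the week-5 score will partly reflect where the patient began. A protein that marks initial severity and has nothing to do with recovery will correlate with the week-5 score. A protein that does relate to recovery has its signal diluted by the spread in starting scores. At stake is the list of proteins reported as recovery markers, which is the product of goal 3.

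**Working it through.** **1. The plan's own figures.** The Power calculations section gives 24 per group, SD 23.5 (motor) and 33 (light touch), two-sided 5%.

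- Two-group t test: 19.5/23.5 = 0.83 SD gives 80.3% power; 27.3/33 = 0.83 SD gives 80.1%.
- Paired t test: 14.1/23.5 = 19.8/33 = 0.60 SD gives 80.4%.
- 60 × 0.80 = 48 completers.

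All reproduce. The paired figures use an SD of change equal to the SD of the score. With equal SDs at both times, SD(change)² = 2·SD²·(1 − ρ), so ρ, the baseline-to-week-5 correlation, is 0.5. This is the document's only hint at ρ, and a weak one. No power or precision is stated for the protein-outcome correlations.

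**2. Which analysis serves goal 3.** Targeted approaches 1 and 2 contain diet, time and peptide but no clinical outcome. Only approach 3 relates peptides to outcomes.

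**3. What the raw correlation estimates.** In SD units let Y5 = ρ·Y0 + √(1 − ρ²)·e, where Y0 is the baseline score and e the part of the week-5 score not predicted by it.

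- Severity-only protein, correlation a with Y0 and none with e: expected raw r = a·ρ; the partial correlation given baseline is 0.
- True recovery protein, correlation 0.40 with e and independent of Y0: expected raw r = 0.40·√(1 − ρ²); the partial correlation is 0.40.

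With n = 48 the 5% critical value is |r| = 2.013/√(46 + 2.013²) = 0.285, and 80% power needs r of about 0.39.

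**4. Simulation.** 20,000 trials per cell, 24 per arm, no diet effect. The comparator is the partial correlation given baseline and diet. The values of a, ρ and the link are assumptions.

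| ρ | Severity-only, a = 0.3: r, raw flagged | Severity-only, a = 0.5: r, raw flagged | True link 0.40: r, raw power | True link 0.40: adjusted power |
|---|---|---|---|---|
| 0.5 | 0.15, 18% | 0.25, 40% | 0.35, 69% | 80% |
| 0.7 | 0.21, 31% | 0.35, 70% | 0.29, 51% | 80% |
| 0.8 | 0.24, 38% | 0.40, 82% | 0.24, 38% | 80% |
| 0.9 | 0.27, 46% | 0.45, 91% | 0.17, 22% | 80% |

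The adjusted test flags the severity-only protein about 5% of the time in every row.

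**5. A change score is not enough.** Under the same model the correlation of a severity-only protein with Y5 − Y0 is −a·√((1 − ρ)/2). For a = 0.5 this is −0.25 at ρ = 0.5 and −0.11 at ρ = 0.9; simulated flag rates are 41% and 12%.

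**6. Diet.** If diet shifts the peptide by dx SD and the outcome by dy SD with no within-arm link, and the arms are pooled, r = (dx·dy/4)/√((1 + dx²/4)(1 + dy²/4)). At the trial's own detectable difference, dx = dy = 0.83, this is 0.172/1.172 = 0.15, flagged 17% of the time. With a peptide shift of 2 SD the rate is 48-49%.

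**The case against.** Several points against the concern are sound.

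- A reader might infer that the correlation is pooled over the diets and so mainly picks up diet. The article does not say pooled, within-arm or adjusted, and a condensed article may leave that to the analysis plan. Even if pooled, the induced correlation with neurological scores is only about 0.15 at the design effect when the peptide shifts equally. Large diet-induced correlations need a large peptide shift or concern metabolic outcomes, which goal 3 does not name.
- A reader might infer that no other analysis relates proteins to patient status. The SWATH-MS section has one. It is untargeted and its phenotypes are undefined, so it does not fill the gap, but the statement must be limited to targeted proteomics. Stratified analyses by injury level are also planned and could remove part of the severity effect. They are not tied to the correlations and would not adjust for baseline score or AIS grade.
- The power loss is not general. It assumes the true marker is independent of baseline. If a marker with a 0.5 link to recovery also correlates +0.4 with baseline, then at ρ = 0.7 raw r = 0.7·0.4 + 0.714·0.917·0.5 = 0.61, which is almost always detected. With −0.4 the same sum is 0.05.
- Adjusting for diet is not plainly right. The Discussion proposes that the ketogenic diet acts partly by lowering fibrinogen, and a diet term removes the between-arm part of that pathway.
- The correlation is described as measuring strength and direction, and no decision rule rests on it.

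None of this removes the mismatch: the method is named, it is the only targeted one with an outcome in it, and it lacks the baseline term that the same section gives the same outcomes in the ANCOVA.

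**Conclusion.** The concern holds in limited form. As written, the targeted-proteomics step for goal 3 measures association with week-5 status, not with improvement, and severity markers can be flagged at several times the nominal 5%. At ρ = 0.5, the value suggested by the plan's paired power figures, the rate is 18-40% for peptide-baseline correlations of 0.3 to 0.5, and the power lost for a baseline-independent link of 0.40 is modest (69% against 80%). The 91% and 22% figures belong to the far end of the assumed range.

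It would go too far to say that goal 3 cannot be answered or that the correlation finds severity instead of recovery: true links are still found, with less power in the case shown. The 5% for the adjusted test assumes that the measured baseline score carries all of the severity signal, which is why AIS grade and injury level belong in the model too. This is a should-fix for the biomarker goal. The randomised diet comparisons, including the ANCOVA and the diet comparisons of peptides, are untouched.

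**What to change.** For the motor, sensory and SCIM outcomes, replace the third approach with a regression of the week-5 score on the peptide level, or the matching partial correlation. Adjust for the baseline value of that score, AIS grade and injury level. Report each estimate with and without diet in the model, and say which question each answers: without diet it includes any between-arm pathway, with diet it is the within-arm link. Keep the raw Pearson correlation as descriptive. Do not use a change-score correlation as the only remedy.

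The cost is a few lines of wording and no new data, since the score, grade and level are already recorded at baseline. The raw correlation has 48 − 2 = 46 degrees of freedom. Baseline score (1), AIS grade (2), cervical or thoracic level (1) and diet (1) take 5, leaving 41, or 42 without diet.

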### Trial monitoring

No regular external trial auditing is scheduled. However, the Data and Safety Monitoring Committee (DSMC) includes two external safety monitors and three study personnel including the PI, study physician and a postdoctoral fellow. Key investigators and study staff provide the DSMC with information regarding safety end points, data quality and validity every 3 months over the course of the study. All human participant data, ranging from recruitment/screening to diet intervention and testing to laboratory tests, are reviewed every 3 months by key study staff, the PI and the DSMC. This includes updates on any new hazards, risks or adverse events, and plans of action. Additional investigators and staff will be asked to participate as the need for their input or expertise arises. If during the course of these meetings particular unforeseen hazards or risks are identified that may predispose to an unusually high number of serious adverse events, the PI consults the appropriate members of the investigative team, as well as the UAB IRB and National Institutes of Health (NIH)/National Institute of Nursing Research (NINR) to determine if the study should be terminated or altered in some way. Any procedure that is deemed hazardous is eliminated from the study and replaced with an alternative if one with reasonable risk can be identified.

### Adverse event monitoring and reporting

#### Reporting

The PI will be responsible for the accurate documentation, investigation and follow-up of all possible study-related adverse events. All adverse events are reported by the PI to the UAB IRB with a description of the event, when and how it was reported, and appropriate documentation to corroborate the event. The description of the adverse event includes all information listed on the case report forms. The IRB then determines whether additional reporting to the NIH/NINR is required.

#### Serious adverse events

All serious adverse events are reported immediately to both the study physician and PI, and then, in turn, reported to the IRB within 48 h. In addition, all serious adverse events that are possibly related to the study intervention are reported to the NIH/NINR within 2 weeks.

#### Nonserious adverse events

Nonserious events are reported to the IRB within 5 business days of the event.

#### Annual reports

An annual statement summarizing the results of safety monitoring is sent to the UAB IRB and to the NIH/NINR. The annual report includes written summaries from quarterly meetings between the DSMC, key personnel and staff, descriptions of all adverse events, and a summary discussing: 1) whether all participants met entry criteria; 2) whether adverse event rates are consistent with expected rates and seriousness; 3) reasons for dropouts from the study; 4) whether continuation of the study is justified; and 5) whether conditions have been met for terminating the study prematurely.

#### Post-trial care

Only minimal risks are anticipated from study participation. Treatment will be provided should adverse events occur but compensation will not be provided for such treatments.

### Protocol amendments

Any change to the protocol requires a written protocol amendment that must be approved by the NIH/NINR and IRB before implementation. Upon acceptance from the sponsor and IRB, the PI makes updates and edits to the study record published on ClinicalTrials.gov. If the PI determines that an immediate change or deviation from the protocol is necessary for safety reasons to eliminate an immediate hazard to the participants, the IRB will be notified immediately.

### Confidentiality

To protect privacy and confidentiality, any original paperwork documenting a participant’s name and PHI is stored in a locked cabinet in the research coordinator’s office, while any digital study records involving PHI are stored in REDCap and/or on computers requiring password authentication that are stored in locked offices and are behind secure firewalls. Records that identify study participants are kept confidential as required by law, and every effort is made to maintain the confidentiality of participants’ study records. Except when required by law or if necessary to protect their rights or welfare, study participants are not identified by name or any other identifying characteristic in records disclosed to those outside of the study staff.

### Access to data

Only study staff, the UAB IRB, official overseers of clinical research at UAB, and representatives of the NIH have access to study records, data and specimens; all access is on a need-to-know basis. All study staff are trained in HIPAA standards for protecting PHI and do not refer to PHI or confidential information in the presence of individuals outside of the study team. Moreover, each study staff member’s access to participants’ data is limited to only the functions for which they are responsible.

### Dissemination policy

The results of our research will be disseminated to three major stakeholders: a) the scientific community; b) individuals with SCI; and c) the general public.

#### a) Scientific Community

The results of this project will be presented at scientific conferences, including at the American Congress of Rehabilitation Medicine, the American Spinal Injury Association and the Society for Neuroscience annual meetings. In addition, results will be published in peer-reviewed journals with open access policies and/or in top-tier journals. The timeline for this is up to 18 months after the last participant completes the study intervention.

#### b) Individuals with SCI

With a timeline of up to 12 months after the last participant completes the study intervention, information will be disseminated to individuals with SCI using the following means.

First, via the UAB Spinal Cord Injury Model System (SCIMS) Information Network website. This website, which averages more than 43,000 visits per year, is newly designed and features a comprehensive collection of links (over 360 to date) to SCI-related information provided by reputable organizations, associations and educational institutions, including from the Model Systems Knowledge Translation Center and other SCIMS centers. The site will be regularly updated with nutrition information and links to other reliable sites of interest and value to SCI consumers. All educational materials written and produced from this project will be made available free on this website.

Second, the UAB-SCIMS newsletter (*Pushin’ On*; now a fully digital newsletter) has been published for 33 years. It provides persons with SCI and their families with information of interest. Over the years, the newsletter has featured original articles along with news, information and synopses of research of importance to individuals with SCI. The study team will work with the newsletter editor to write a synopsis of the proposed research trial, including a description of the diet intervention and a lay summary of major findings and how to implement them.

Finally, for more than 60 years, *Paraplegia News* has been a leader in the wheelchair community for pertinent practical news and information. Paraplegia News Online is an extension of *Paraplegia News* that is easily accessible on the worldwide web and that is dedicated to bringing the very best of real-time, up-to-the-moment news and information for wheelchair users, family members and medical professionals on the go. The study team will work with the newsletter editor to write a synopsis of the proposed research trial including the description of diet intervention and a lay summary of major findings and how to implement them.

